#### Secondary endpoints

The secondary endpoints include: (1) myocardial injury (as defined earlier); (2) morbidity 2–3 and 6–7 days after surgery, as defined by the POMS; (3) absolute concentrations of serum high-sensitivity troponin T measured on day 1, 2, and 3 after surgery; (4) mortality within 180 days from surgery; and (5) predefined complications at day 30 after surgery graded using the Clavien–Dindo classification.^31^

### Planned process measures

The planned process measures include (1) duration of hospital stay from surgery (number of calendar days from surgery until hospital discharge) and (2) number of calendar days requiring critical care admission (level 2 and 3) up to 30 days from surgery.

### Assessment of outcomes after hospital discharge

Participants discharged from hospital before day 30 will be contacted shortly after day 30 to establish any additional healthcare encounters since discharge, including hospital readmission. For participants who have received further treatment or seen a health professional since discharge, further details will be collected directly from the hospital/doctor or from the participant's health records. Mortality will be established by a participant medical record review, data from NHS Digital for participants in UK sites, or both. Morbidity outcomes will be assessed by a review of the participant's medical records, and by telephone interview in the same way as the primary outcome for 30-day outcomes.

### Protocol compliance monitoring

The tablets will be taken by the patient in the presence of a member of the direct clinical care team who will ensure that all required tables are swallowed. The number of tablets administered and the time of administration will be recorded on the electronic case report form (eCRF). If an incorrect number of tablets are administered or a dose is missed, a protocol deviation form will be completed.

### Safety and predefined adverse events

Safety data will be reported based on reviewing the patients' medical records and discussion with the patient. As ivabradine is already licenced and well-studied in the target age group, only certain safety events as outlined below will be collected as part of the trial procedures. Owing to the specificity of ivabradine on the sinoatrial node, only events specific to the drug action are recorded. It is expected that patients undergoing noncardiac surgery may often suffer from medical complications, up to and including death. As a result, a large number of participants will experience complications after surgery, which are completely unrelated to the trial intervention. These surgical complications will be recorded separately as part of outcome data.

Pharmacovigilance reporting will start from the completion of informed consent and stop no earlier than on day 30, the last day of talking to the patient. This will require either (1) review of the participant's medical notes if in hospital or (2) daily telephone call with the participant. In the event the research team is unable to speak with the participant, their general practitioner will be contacted. Although the events listed below are often observed in high-risk surgical patients, they will serve as safety outcome measures for the trial: (1) bradycardia <45 beats min^−1^ requiring rescue therapy according to local hospital guidelines, pacing detected as part of routine clinical care within the first 6 postoperative days, or both; (2) atrial fibrillation detected as part of routine clinical care within the first 6 postoperative days; (3) tachycardia >100 beats min^−1^ requiring treatment as recorded clinically within the first 6 postoperative days; (4) hypotension (MAP <60 mm Hg) detected as part of routine clinical care requiring pressor infusion within the first 6 days postoperative days; and (5) phosphenes (the experience of seeing light without light actually entering the eye) within the first 6 postoperative days.

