The precedent for cardiac tissue injury fuelling distant organ dysfunction (and hence morbidity) is well established in experimental models of immunosuppression after tissue injury. Murine cardiac dysfunction after experimental myocardial infarction increases susceptibility to bacterial infection owing to impaired phagocytosis in hepatic macrophages.^35^ Lymphopaenia is a prototypical response after tissue injury, triggered by a hyperacute pro-inflammatory response after disparate sites of organ injury.^36^ Cell-free DNA released by tissue injury binds to the inflammasome activator absent in melanoma 2 (AIM2) in myeloid cells.^37^ In turn, AIM2 inflammasome-dependent interleukin-1β secretion by monocytes leads to extrinsic T-cell apoptosis. In support of these observations, clinical myocardial injury and complications are independently associated with a lower absolute preoperative lymphocyte count^38^ and a higher absolute preoperative monocyte count.^5^

In the general population, lower resting heart rates are protective against cardiovascular pathology.^39^ Heart rate is a key determinant of the balance between myocardial oxygen supply and demand.^40^ However, lowering the heart rate before noncardiac surgery using negative chronotropic agents such as beta-blockers shows that off-target effects of reducing oxygen demand can be counterproductive.^14^ It is likely that fixed doses of heart rate-lowering therapy that are not titrated to a target heart rate threshold are detrimental through hypoperfusion after profound hypotension.^14^ Although preoperative heart reduction may therefore be beneficial, excessive reductions therefore appear very likely to be harmful.^41^ Moreover, if elevated perioperative heart rate serves merely as a marker of vagal autonomic impairment, a strategy of reducing heart rate may actually be harmful.

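### Bradycardia below 45 is a safety outcome only if it requires rescue under local guidelines or pacing, so untreated slowing falls outside the safety outcomes and its absolute excess may be under-reported

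*Protocol article*

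**What the plan says.** All of the following is in the protocol article.

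- **Definition** (Safety and predefined adverse events): the first listed safety outcome is "bradycardia <45 beats min^−1^ requiring rescue therapy according to local hospital guidelines", or pacing found in routine care, or both, within the first six postoperative days.
- **Scope** (same section): the list is closed, since "only certain safety events as outlined below will be collected as part of the trial procedures". The reason given is that the drug is licensed and well studied, and that "only events specific to the drug action are recorded".
- **Other items on the list:** two more depend on treatment. Tachycardia counts as "tachycardia >100 beats min^−1^ requiring treatment as recorded clinically within the first 6 postoperative days", and low mean arterial pressure counts when "detected as part of routine clinical care requiring pressor infusion". Atrial fibrillation and phosphenes need no treatment to count.
- **Heart rate readings** (Study interventions): resting heart rate is taken in the hour before each of six administrations over three days. The lowest value decides the number of tablets, and Table 2 gives none when it is under 70. The section adds that the pilot study showed this individualised dosing to reduce the risk of bradycardia.
- **Sites** (Setting; Study design): three hospitals in an international trial.

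**The concern.** The drug lowers heart rate, and the article justifies its short safety list as holding events specific to the drug's action. Excess slowing is the direct extension of that action, yet it enters the safety outcomes only through a treatment decision. Take a participant with a resting rate of 40 before the fourth administration. Under Table 2 no tablet is given. If no rescue or pacing is required, no safety event arises, although the reading has been taken.

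The requirement for rescue is set by each hospital's own guideline, so the same heart rate can be an event at one site and not at another.

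What is at stake is the description of harm. The article says the dosing scheme lowers the risk of bradycardia, and its Discussion says of heart rate lowering in general that "excessive reductions therefore appear very likely to be harmful". A safety table confined to treated episodes cannot show how often the scheme overshoots. A low count could mean that slowing was rare, or that it was common but seldom treated.

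**Working it through.** **What can be reproduced.** The article gives no bradycardia rate, so there is no plan figure to check on this point. The only design number needed is the arm size. The stated 173 per arm with 1% dropout gives 173 / 0.99 = 174.7, rounded up to 175, or 350 in total, as stated.

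**Effect of the treatment condition.** Let p be the true proportion of an arm with any heart rate below 45, and f the fraction of those participants whose episode requires rescue or pacing.

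- Expected counted events per arm = 175 × p × f
- Counted risk difference = p(iva) × f(iva) − p(plac) × f(plac), which equals f × [p(iva) − p(plac)] when f is the same in both arms
- Counted risk ratio = [p(iva) / p(plac)] × [f(iva) / f(plac)], which does not depend on f when f is the same in both arms

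**Illustration.** Every p and f below is an assumption; none comes from the article. Cells give expected counted events per 175 (ivabradine v placebo), then the risk difference in percentage points.

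| Assumed true rates | f = 1 | f = 0.5 | f = 0.25 | f = 0.1 | Risk ratio |
|---|---|---|---|---|---|
| 5% v 1% | 8.8 v 1.8; 4 | 4.4 v 0.9; 2 | 2.2 v 0.4; 1 | 0.9 v 0.2; 0.4 | 5 |
| 10% v 2% | 17.5 v 3.5; 8 | 8.8 v 1.8; 4 | 4.4 v 0.9; 2 | 1.8 v 0.4; 0.8 | 5 |
| 15% v 5% | 26.3 v 8.8; 10 | 13.1 v 4.4; 5 | 6.6 v 2.2; 2.5 | 2.6 v 0.9; 1 | 3 |

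For example, 10% v 2% at f = 0.25 gives 175 × 0.10 × 0.25 = 4.4 and 175 × 0.02 × 0.25 = 0.9, with a difference of 0.25 × 8 = 2 points.

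The absolute excess falls in direct proportion to f, and the ratio is unchanged along each row. As f cannot be obtained from the article, the size of the under-reporting cannot be either.

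**Are the data for a fuller count available?** There are six scheduled pre-dose readings. The first precedes any study drug and is a baseline value, which leaves 6 − 1 = 5 readings that can reflect treatment. They stop on the evening of the second postoperative day, while the safety window runs to day six. They also fall before each dose, so slowing between doses can be missed. They are nevertheless scheduled identically in both arms and at every site, and they do not depend on a decision to treat.

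**The case against.** The strongest reply is that this is a deliberate severity threshold, not an error. Tachycardia and hypotension are handled in the same way, and the article gives its reason for a short list. That stands: the definition contradicts nothing and need not be replaced. It does not answer the narrower point that the threshold is the only bradycardia measure among the safety outcomes.

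A second reply is that low pre-dose rates are observed and may be tabulated under the statistical analysis plan or the supplementary data schedule, neither of which is shown. That also stands. A reader might infer that untreated bradycardia goes wholly unrecorded, but the article supports only that it lies outside the listed safety outcomes.

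A third concerns bias. A reader might infer that the comparison is tilted towards ivabradine. Treating staff and assessors are blinded and site is a minimisation variable, so guideline differences among hospitals should be roughly balanced between arms. Blinding does not guarantee equal f. If drug-induced slowing came without hypotension, as the article's account of the pharmacology might suggest, it could be rescued less often than placebo-arm bradycardia. With assumed true counts of 14 v 5 and 25% v 75% rescued, 3.5 v 3.75 would be counted. That shows bias is possible; nothing in the article shows that it occurs.

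Two further inferences fail. The article does not call bradycardia the main expected harm, and its remark on excessive reductions follows a discussion of beta-blockers and untitrated fixed doses. Nor does treated tachycardia cancel bradycardia in the safety profile: the five events are listed separately and never combined.

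**Conclusion.** The point holds as a limitation of a fixed definition that is cheap to remedy. Followed as written, the safety outcomes exclude any heart rate below 45 that requires neither rescue nor pacing, and the trigger may vary among the three hospitals. The absolute excess of slowing on ivabradine may therefore be under-reported by the factor f, which is unknown. If f is equal across the blinded arms, the risk ratio is preserved. Between-arm bias is not shown.

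This rests on reading the list as closed, which the section states, and on taking the word requiring at face value: an episode that does not meet the local guideline is not an event. The illustrated rates are assumptions and carry no evidential weight.

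**What to change.** Leave the rescue-or-pacing outcome as defined. In the statistical analysis plan, unless already there, add a safety table by randomised arm of the number and proportion of participants with any pre-dose resting heart rate below 45 beats per minute, whether or not treated.

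- Show the first reading separately as baseline, since it precedes study drug.
- Include readings from occasions when Table 2 led to no tablet.
- State how many participants contribute a reading at each time, and give the rescue-or-pacing subset alongside.
- List separately any value below 45 noted in the medical-record review already carried out for safety.

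The pre-dose table should be the main one, because chart values depend on how closely a patient is monitored and so vary by ward and site.

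The cost is low. The pre-dose readings are already required for dosing, although the article does not say that the values themselves are entered on the electronic case report form, so this should be confirmed. Recruitment is due to end in 2025, so a new retrospective chart search would be a larger task and is not needed. The downside is that more asymptomatic episodes will be reported. This is a reporting change only and alters no dose or clinical rule.

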### Study interventions

Usual perioperative care will proceed in each centre for participants in this trial. Blood samples will be collected and prepared for serum and plasma before surgery, 24, 48, and 72 h after surgery, between 06:00 and 10:00, before freezing at –80°C, thus maintaining blinding of the primary outcome. Measurement of high-sensitivity troponin in batched frozen samples stored for 928 days does not affect the results providing values indistinguishable from ‘on-demand’ fresh samples (including using these results for the clinical application of rapid diagnostic algorithms).^28^

Before dosing, resting heart rate and orthostatic heart rate changes from sitting to standing are recorded, which quantify cardiac vagal activity.^29^ Participants receive 0–3 tablets that are indistinguishable, being either 2.5 mg of ivabradine or placebo, based on the participant's resting heart rate within 1 h before dosing (Table 2), unless MAP is <60 mm Hg or a new-onset arrhythmia has been recorded. If multiple heart rate measurements have been recorded within 1 h before dosing, the lowest value is taken to determine the dose of the investigational medicinal product (IMP). Dosing is performed by research staff and will occur twice daily from the morning of surgery until the evening of postoperative day 2 (3 days, six administrations). The individualised variable dosage has been shown in our pilot study to achieve the target heart rate of 60–70 beats min^−1^ while decreasing the risk of bradycardia (Table 1).

**Table 2 tbl2:** Protocol for administration of investigational medicinal product, according to heart rate.

Heart rate(beats min^−1^)	Ivabradine or placebo(identical tablets)
<70	Omit
70–84	1 tablet (2.5 mg if ivabradine)
85–100	2 tablets (5 mg if ivabradine)
>100	3 tablets (7.5 mg if ivabradine)

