### Statistical analysis

A full statistical analysis plan will be developed before any interim or final analysis and published online at https://www.qmul.ac.uk/ccpmg/sops--saps/statistical-analysis-plans-saps/. During the recruitment period, the trial statistician will perform a safety analysis if specifically requested by the DMEC, as outlined in the DMEC charter.

All analyses will be conducted according to the intention-to-treat principle, with all randomised participants with a recorded outcome analysed according to the treatment to which they were randomised. The primary outcome will be analysed using a logistic regression model. The model will be adjusted for minimisation variables (trial centre and planned surgical procedure [surgery involving the gut, all other surgery]). The model will also be adjusted for pre-specified baseline covariates entered into the model as fixed factors. Preoperative heart rate before the first IMP administration will be included as a continuous variable, assuming a linear association with the outcome. The magnitude of the treatment effect will be reported as an adjusted odds ratio (OR) with a 95% confidence interval (CI). Significance will be set at *P*<0.05. Similar analyses of secondary outcomes will be undertaken by intention-to-treat principle, according to the treatment to which they were randomised.

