The strengths of this phase 2 RCT are that patients, investigators, and clinical teams will be blinded through the use of placebo tablets. Participants and clinicians will be blinded to both treatment and the troponin results. Heart rate changes during the intervention period (surgery day to postoperative day 2) are dynamic and influenced by multiple factors. Non-IMP interventions remain unrestricted. In our prior pilot trial with the same heart rate-guided ivabradine or placebo intervention, clinical staff identifying which trial arm patients were allocated did not emerge as an operational issue for the execution of FUNNY.^26^ The multicentre, international design and broad inclusion criteria are generalisable to a larger number of patients undergoing noncardiac surgery and therefore address a major healthcare burden of clear importance to patients.

In summary, this phase 2b study will establish whether targeted heart rate control reduces morbidity after surgery associated with early myocardial injury, using ivabradine to selectively slow the heart rate without impairing perioperative haemodynamic control.

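### Four of the five safety outcomes are counted only from the postoperative days, although dosing starts on the morning of surgery and pharmacovigilance starts at consent; the three windows need reconciling

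*Protocol article*

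**What the plan says.** Three time windows bear on this point in the protocol article.

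- **Dosing** (Study interventions): "Dosing is performed by research staff and will occur twice daily from the morning of surgery until the evening of postoperative day 2". The text counts this as three days and six administrations. Table 2 omits the dose when heart rate is below 70 beats per minute.
- **Pharmacovigilance** (Safety and predefined adverse events): "Pharmacovigilance reporting will start from the completion of informed consent and stop no earlier than on day 30". Enrolment places consent on the day of surgery, and Randomisation follows it.
- **Safety outcomes** (Safety and predefined adverse events): five listed events serve as the trial's safety outcome measures. Hypotension is "hypotension (MAP <60 mm Hg) detected as part of routine clinical care requiring pressor infusion within the first 6 days postoperative days". Atrial fibrillation, tachycardia and phosphenes carry the same limit. Bradycardia below 45 beats per minute is worded differently: "requiring rescue therapy according to local hospital guidelines, pacing detected as part of routine clinical care within the first 6 postoperative days, or both".

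The same section says that "only certain safety events as outlined below will be collected as part of the trial procedures".

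**The concern.** The first exposure to the drug appears to coincide with anaesthesia and operation, while the window for most safety outcomes opens only afterwards. An outcome window should normally open at first exposure, so that the randomised comparison covers the whole period in which the drug could do harm.

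This period matters to the trial's own argument. The introduction contrasts ivabradine with beta-blockers and clonidine, which it says led to hypotension. The Discussion warns that excessive heart rate reduction is likely to be harmful, and its closing sentence presents ivabradine as slowing the heart without impairing haemodynamic control around surgery. A comparison that leaves out the operation cannot test that statement for the operation. Because the article does not say how the windows fit together, sites could also classify the same intraoperative event differently.

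**Working it through.** The article attaches no computed figure to this point. Its only calculation, the sample size, concerns the primary endpoint. The check is therefore to place the windows on one time line.

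**1. Is the first dose given before surgery?** This is not stated outright, but three sections point the same way.
- Study interventions starts dosing on the morning of surgery and records the sitting-to-standing heart rate change before dosing.
- Protocol compliance monitoring has the patient swallow the tablets under observation.
- Statistical analysis says "Preoperative heart rate before the first IMP administration will be included as a continuous variable".

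A preoperative first dose is a sound inference from these.

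**2. Is the surgery day a postoperative day?** The Discussion gives the intervention period as follows: "Heart rate changes during the intervention period (surgery day to postoperative day 2) are dynamic and influenced by multiple factors". The dose count agrees that the surgery day is separate:
- Surgery day = day 0: days 0, 1 and 2 at two doses a day give 3 × 2 = 6 administrations, as stated.
- Surgery day = postoperative day 1: days 1 and 2 give 2 × 2 = 4 administrations, not six.

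So in the article's own numbering the surgery day comes before postoperative day 1.

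**3. The time line.**

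| Time | Dosing | Pharmacovigilance | Outcome window, postoperative days 1–6 | Outcome window, from end of surgery to day 6 |
|---|---|---|---|---|
| Consent, day of surgery | none yet | open | closed | closed |
| Morning of surgery | dose 1 | open | closed | closed |
| During surgery | exposed if dose 1 was taken | open | closed | closed |
| Evening of surgery | dose 2 | open | closed | open |
| Postoperative days 1–2 | doses 3–6 | open | open | open |
| Postoperative days 3–6 | none | open | open | open |
| To day 30 or later | none | open | closed | closed |

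**4. What falls before the window.** On the calendar-day reading, 2 of 6 scheduled administrations (33%) are given before it opens, and the whole surgery day is left out. On the looser reading, 1 of 6 (17%) is given before it opens, and the interval from dose 1 to the end of surgery is left out. Both readings leave out the operation. These are scheduled doses: a participant with a heart rate below 70 takes no tablets at that time point.

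**5. Item by item.**
- Hypotension, atrial fibrillation, tachycardia and phosphenes: the window qualifies the event directly, so intraoperative events are outside it.
- Bradycardia: the window phrase follows pacing. If it covers both limbs, intraoperative bradycardia needing rescue therapy is outside. If it covers pacing alone, that bradycardia is inside, but its limb then has no stated start or end. The text does not settle which is meant.

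**The case against.** The strongest reply is that pharmacovigilance opens at consent, with review of the medical notes, so intraoperative events are captured. The restriction to certain listed events limits the type of event, not its timing, and the six-day phrase could be read as an end limit on a period already open. It is true that the reporting period covers surgery. But the listed events are the ones that serve as safety outcome measures, and the window is part of their definition. Being reportable does not make an event countable. That another reading is possible is a reason to reconcile the text.

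A second reply is that this is a condensed article, and the full protocol or the supplement may define the days. That lowers certainty. Still, the window is stated explicitly here, and it does not match the dosing period stated in the same article.

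A third is that a postoperative window may be deliberate for hypotension, because intraoperative pressor use is likely to be common in both arms and could swamp the comparison. That is a fair reason to show the periods separately. The article does not give it as a reason for leaving the operation out.

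A reader might infer three stronger things that the documents do not support:
- **That intraoperative bradycardia is definitely uncounted.** The wording is ambiguous, as shown under the working.
- **That the data monitoring committee would be misled.** Data monitoring gives it safety oversight, and Statistical analysis lets it request a safety analysis. Neither confines it to the five windowed outcomes.
- **That a given number of harms would be missed.** No safety event rates are given, and Table 2 means that an unknown share of participants takes no first dose, so 175 per arm is not the number exposed at surgery.

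**Conclusion.** The point holds as an unreconciled mismatch between three windows. Read literally, hypotension, atrial fibrillation, tachycardia and phosphenes between the first dose and the end of surgery (or on the whole surgery day) fall outside the safety outcome comparison, and pressor-treated hypotension is the clearest case. For bradycardia needing rescue therapy, the article leaves the matter open.

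In terms of exposure, one or two of the six scheduled administrations precede the window, depending on the reading. The number of events affected cannot be derived from the documents. The conclusion assumes that the first dose is preoperative, which is inferred, and that the full protocol does not define the days differently. The primary analysis and sample size are untouched. The change is worth making because the gap covers the first period of exposure and could understate harm in the final safety comparison.

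**What to change.** Reconcile the three windows in Safety and predefined adverse events:

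1. Define all five safety outcomes from first administration of study drug to the end of postoperative day 6. For participants whose first dose is omitted, start at randomisation. If omission and first administration can fall at different times, randomisation as the common start for everyone is the simpler rule for an intention-to-treat comparison.
2. State that the surgery day is included and is day 0.
3. Reword the bradycardia item so that the window plainly covers both rescue therapy and pacing.
4. Report bradycardia and hypotension separately for the intraoperative and postoperative periods, taking intraoperative events from the routine anaesthetic record.

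This changes what is counted, not any dose or clinical rule. The cost is some additional record review, including for participants already enrolled, since recruitment began in January 2022. The section already relies on medical-record review for safety data, so no new type of data source is needed. Intraoperative pressor use is likely to be common in both arms and could dilute a pooled comparison, hence the separate display. The definition should be settled before unblinding.
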